## Abstract

**Background:**

Interventions to support people with hypertension in attending clinics and taking their medication have potential to improve outcomes, but delivery on a wide scale and at low cost is challenging. Some trials evaluating clinical interventions using short message service (SMS) text-messaging systems have shown important outcomes, although evidence is limited. We have developed a novel SMS system integrated with clinical care for use by people with hypertension in a low-resource setting. We aim to test the efficacy of the system in improving blood pressure control and treatment adherence compared to usual care.

**Methods/design:**

The SMS Text-message Adherence suppoRt trial (StAR) is a pragmatic individually randomised three-arm parallel group trial in adults treated for hypertension at a single primary care centre in Cape Town, South Africa. The intervention is a structured programme of clinic appointment, medication pick-up reminders, medication adherence support and hypertension-related education delivered remotely using an automated system with either informational or interactive SMS text-messages. Usual care is supplemented by infrequent non-hypertension related SMS text-messages. Participants are 1:1:1 individually randomised, to usual care or to one of the two active interventions using minimisation to dynamically adjust for gender, age, baseline systolic blood pressure, years with hypertension, and previous clinic attendance. The primary outcome is the change in mean systolic blood pressure at 12-month follow-up from baseline measured with research staff blinded to trial allocation. Secondary outcomes include the proportion of patients with 80% or more of days medication available, proportion of participants achieving a systolic blood pressure less than 140 mmHg and a diastolic blood pressure less than 90 mmHg, hospital admissions, health status, retention in clinical care, satisfaction with treatment and care, and patient related quality of life. Anonymised demographic data are collected on non-participants.

**Discussion:**

The StAR trial uses a novel, low cost system based on widely available mobile phone technology to deliver the SMS-based intervention, manage communication with patients, and measure clinically relevant outcomes. The results will inform implementation and wider use of mobile phone based interventions for health care delivery in a low-resource setting.

**Trial registration:**

NCT02019823

## Background

Globally, high blood pressure is the leading single risk factor for cardiovascular and related diseases [1,2]. Individual patient-level data have shown that usual blood pressure is “strongly and directly” associated with cardiovascular and overall mortality risk [3], and that lowering blood pressure reduces this risk [4-6]. Controlling blood pressure at a population level may be associated with a decrease in cardiovascular disease regardless of the increasing burden of obesity and diabetes [7]. The burden of disease associated with hypertension is greatest in low-resource settings [2,8], where there is a need for better control of blood pressure [9,10].

Treatment to lower blood pressure includes drug and non-drug measures as well as modification of known life-style associated risk factors, such as smoking and alcohol intake [6,11,12]. Long-term blood pressure control requires integrating medication taking into daily life to support adherence and persisting with treatment.

A wide range of different strategies and interventions has been used to support patients in adhering to treatment plans, although results are not consistent [13]. One strategy that may facilitate such support is the integration of a patient’s mobile (or cellular) phone in the process of health care delivery. Globally, the mobile phone has become the preferred tool for communication and access to information bringing together communication and computing technology. Mobile-phone-based interventions could address individual-level factors in health by facilitating timely patient access to relevant health information and support, making patient-provider communication easier, and providing context-specific support and prompts to action [14].

Despite widespread interest in the potential for mobile phone based interventions to deliver disease management and health-related behaviour change sustainably and at scale, published evidence of effectiveness is limited [15]. SMS-text messages are available on all mobile phone platforms and with all providers. Text messages have the potential to provide information alone (informational) or provide two-way communication (interactive or bi-directional). Some but not all trials suggest that SMS text-message reminders may improve clinic attendance, retention in care, and self-reported medication adherence [15]. Two trials in Spain with short follow-up periods have explored the efficacy of SMS-based interventions for people with hypertension to improve treatment compliance and blood pressure control. Although the trials results suggest potential for small to moderate effect sizes in improved compliance and blood pressure control, the effects were not statistically significant [16].

## Methods

### Design and hypothesis

The SMS Text-message Adherence suppoRt trial (StAR) is a twelve-month, pragmatic three-arm parallel group trial. Participants are individually randomised to one of two trial intervention groups or an enhanced usual care group (control) in a 1:1:1 allocation ratio (Figure 1).

**Figure 1 F1:**
[figure not shown]
CONSORT diagram for SMS-text Adherence suppoRt Trial (StAR).

We therefore plan to test whether a structured intervention delivered by an automated system of SMS text-messages providing clinic appointment and medication pick-up reminders, medication adherence support and hypertension-related education delivered remotely through informational or interactive SMS text-messages is more effective than usual care in controlling blood pressure.

### Setting

Participants are recruited from the Vanguard Community Health Centre, a public sector, large primary care clinic in Bonteheuwel, Cape Town, South Africa, serving two diverse low-middle income communities, Langa and Bonteheuwel. The health centre provides a full range of primary care services with approximately 28,000 people attending each month. The “chronic diseases of lifestyle clinic” services a caseload of about 500 patients per week. Patients with hypertension are managed by nurse practitioners and doctors in structured clinics. The local Department of Health provides medications for the treatment of hypertension in line with national and international hypertension management guidelines [17]. Medications are provided either pre-packed from an off-site pharmacy, or dispensed on-site. Medications are usually provided for 28 days. Patients are required to attend the clinic monthly to collect their medication. There is no fee for receiving care or medication in primary care.

### Participants

Trial eligibility criteria are: (i) a clinical diagnosis of hypertension and either currently receiving blood pressure lowering medication or are about to start such medication, (ii) a systolic blood pressure <220 mmHg and a diastolic blood pressure <120 mmHg at enrolment (iii) aged 21 years or older, (iv) own or have daily access to a cell-phone, (v) able to send a SMS text-message, or can do so with help of a relative, (vi) do not live in a household where another member has been recruited into the trial, (vii) not pregnant or within three months post-partum by self-report, (viii) currently residing in the trial area and expecting to be resident for the duration of the trial and (ix) willing to give informed consent to take part in the trial. Patients with a systolic blood pressure >175 mmHg or a diastolic blood pressure >105 mmHg are eligible only if they have no symptoms suggesting a hypertensive emergency and they have been evaluated by a medical officer.

### Interventions

The two active interventions are delivered by an automated system of SMS text-messages providing clinic appointment and medication pick-up reminders, medication adherence support and hypertension-related education delivered remotely using either informational or interactive SMS text-message.

#### Intervention development

We iteratively designed, developed, and tested the interventions using a formal process to synthesise existing evidence, the opinion of clinical staff, and patients with chronic diseases (Figure 2). [18,19]As part of this process we developed a bank of SMS-text messages which we mapped on a taxonomy of behaviour change techniques. [20] Most of the content focused on the techniques of goals and planning, repetition and substitution, social support, and natural consequences (Table 1). The SMS text-messages used in the intervention were developed, translated, and tested in English, Afrikaans and isiXhosa, the three languages most commonly spoken by people living in Cape Town.

**Figure 2 F2:**
[figure not shown]
**Process of intervention development adapted from Smith et al. [**[18]**].**

**Table 1 T1:** Examples of trial text messages mapped to behavioural change taxonomy

Goals & planning	A pill box can help you to remember when to take you high blood pills. We encourage you to get one. For more info ask PHARMACY.
	Make taking your pills part of your daily routine, like when you brush your teeth. Doing this can help you remember to take them regularly.
Repetition & substitution	Pls remember your next CLUB DATE is on [DAY][DD/MM/YY] at [TIME].
	Thnx for picking up your meds. Keeping on your pills & attending on your correct dates helps us serve you better.
	We missed you @ CLUB. We hope you’re OK. Pls be sure to come in to collect your MEDICINE.
Social support	Ask someone you trust to help you remember to take your medicine as directed.
	You’re doing very well. Pls keep on with your pills, come on your clinic dates, exercise&eat healthy food.
Natural consequences	Pls remember your high blood can’t be cured. To keep healthy pls keep on with your pills, come on your clinic dates, exercise&eat healthy food.

#### Informational (unidirectional) SMS text-message system

Participants allocated to the informational SMS text-message group receive an intervention that includes reminders about medication collection, scheduled clinic appointments and follow-up text-messages (including reminders when medicines are not collected), and a SMS-text promoting specific adherence-related behaviours. The SMS-texts are sent weekly at a time and in a language selected by the participant. Some of the texts are personalised (include first or chosen name). The intervention is compliant with South African regulations and ethics, and regulatory guidelines on good SMS-practice [21].

#### Interactive (bidirectional SMS text-message reminders)

In addition to the intervention provided to participants allocated to the informational SMS text-message group, participants in the interactive SMS text-message group can also respond to texts and send messages to the clinic. For example, when appointment reminders are sent to participants in the interactive SMS text-message group, they will include an option to reply if they cannot make their scheduled appointment and to cancel or change their appointment as necessary. Examples of the type of SMS text-messages sent to participants allocated to the two intervention arms are shown in Table 2.

**Table 2 T2:** Examples of intervention group SMS-text messages in English

• **Appointment reminder SMS-texts**	*Hi [insert name]. Pls remember your next MEDICINE DATE is on [DAY][DD/MM/YY] at [TIME]. Thnx Dr [NAME] (DR@VAN)*
• **In response to missing a scheduled appointment**	*We missed you @ PHARMACY. We hope you’re OK. Pls be sure to come in to collect your MEDICINE. Thnx Dr [NAME] (DR@VAN)*
• **Messages related to specific issues**	*A pill box can help you to remember when to take your high blood pills. Ask at PHARMACY where you can buy one. Thnx Dr[NAME](PHARM@VAN)*
	*Pls be sure to take all your medicine as directed even if you feel well. Thnx Sr [NAME](SR@VAN)*
	*Pls tell us(DR&PHARMACY)if you think your high blood pills are making you feel unwell. Ask us about common side effects of your pills. Thnx Dr [NAME](DR&PHARM@VAN)*

#### Usual care

Participants allocated to the usual care group only receive the SMS-texts sent to all trial participants. These messages are sent no more frequently than one SMS text-message every four weeks. The messages are a welcome SMS text-message, a text confirming enrolment, an SMS text-message on a birthday, and other SMS text-messages about participation in the trial. Examples of the types of SMS texts-messages sent to all trial participants can be seen in Table 3.

**Table 3 T3:** Examples of trial-specific group-text messages in English

**• Welcome SMS-text message**	*Welcome to StAR* thank you for participating. The trial cell is 0XXXXXX120 (save on phone). We will never ask for personal or banking details. Dr[NAME](StAR*@VAN)*
**• Trial specific SMS-texts**	*Pls remember your participation in StAR* is voluntary. Call, text, or send plz cal 0XXXXXX372 (its free) if you need to withdraw. Thnx Dr [NAME] (StAR*@VAN)*
	*Pls remember participating in StAR is free. We do not charge you for the SMS-texts we send to you. Thnx Dr [NAME] (StAR@VAN)*
**• Birthday SMS-text**	*Hi [NAME]. Happy birthday, have a great day. Thnx [NAMES](Health Team & StAR*@VAN)*

### Procedures to promote intervention fidelity and reduce between-group contamination

Clinic staff and trial participants are told that the trial procedures involve collecting information about the number, timing, and content of text-messages for health and thus not everyone will be receiving the exact same number or type of messages. Participants are asked not to share the SMS text-messages with others. SMS text-message content is stored remotely in a message bank on a secure server. An automated delivery system is used to send SMS text-messages and to manage interaction with trial participants at no cost to participants (Table 4). The server and delivery system are managed by technicians with no direct contact with trial participants. Trial staff are clearly identifiable and distinct from clinic staff. A trial log is kept to record and describe any unscheduled contact between trial participants and the trial team.

**Table 4 T4:** Practical aspects of sending and receiving SMS text messages

**SMS text message**	• Receiving SMS text messages or phone calls is free in South Africa
	• SMS text messages can be sent to participants through any of the local mobile phone network providers
**“Please Call Me” (PCM)**	• PCM messages are equivalent to a missed-call and are freely available (a minimum of five PCMs are available daily) across all local networks
**Devices or credit**	• Participants are not be provided with mobile phones or network airtime credit

### Outcomes

#### Primary outcome measures

The primary clinical outcome is change in mean systolic blood pressure from baseline to twelve months measured with a validated electronic device (IEM Stabil-o-graph©) using a standard protocol [22]. We record six sequential blood pressure readings at 3-minute intervals. Data from the IEM Stabil-o-graph© are uploaded to trial database and the reported blood pressure is calculated by discarding the initial reading and calculating the mean from the five remaining readings. [23]

#### Secondary outcomes

Treatment adherence is assessed by calculating the proportion of days of medication covered from routinely collected prescribing and dispensing data obtained during the 12-month follow-up period [24]. Data will be reported in three-monthly intervals. Adherence will be reported as the proportion of patients with ≥80% of days covered with medication [25], and as a continuous measure.

Additional secondary outcomes are: proportion of participants achieving a systolic blood pressure less than 140 mmHg and a diastolic blood pressure less than 90 mmHg, and health status measured with the EuroQol 5-Dimension and Visual Analogue Scale measures [26], proportion of scheduled clinic appointments attended, retention in clinical care, satisfaction with clinic services and care using 12 five-point Likert-scale items adapted from locally appropriate questionnaires developed to capture patient satisfaction with services for HIV-care, [27,28] hospital admissions, a Visual Analogue Scale for self-reported adherence to medication, and an adapted four-point scale evaluating basic hypertension knowledge. [29] We are also collecting data on the number and type of medication changes made during the trial and reported side-effects of medication. Anonymised demographic data are collected on non-participants.

### Trial procedures

The trial specific procedures to recruit, enrol and follow-up participants are integrated within existing health care delivery pathways. Participants continue to receive clinical care from their usual care providers.

#### Baseline data collection

Participants are recruited from patients attending any of the chronic disease services at the health centre. Potential participants are given information (verbal and written) about the trial and, if willing, screened for eligibility. All trial information is available in English, isiXhosa, and Afrikaans. The trial screening protocol includes the standardised measurement of height, weight, waist circumference, and blood pressure using a validated electronic device and the data are entered into the patient’s clinic record. Eligible individuals interested in participating have the opportunity of asking trained research staff further questions about the trial and sufficient time to consider whether or not they wish to participate.

Consenting participants attend a baseline consultation of 20 minutes with a trained research assistant. After obtaining written confirmation of informed consent and detailed contact information including the participant’s mobile-phone number, the data are uploaded and the system sends a “Welcome” SMS-text message to the participant, allowing further discussion of the SMS-based support that will be available in the trial. Participants select the language, and the day and time of the SMS-messages they will receive. No further specific training is given in how to access or interpret the message. Confirmed receipt of the SMS-text (either in real-time or within 72 hours of registration) is a required for completion of the enrolment procedure and trial randomisation. The research assistant then administers a short baseline questionnaire; details of current clinical management and medication are extracted from paper-based and electronic records from the clinic and other Department of Health service providers.

#### Follow up to 12 months

Trial participants are followed upwhen they attend for planned clinic appointments. Data on scheduled clinic appointment attendance, prescription refill collection, and drug availability are extracted from routinely collected service-delivery data. At the six-month visit participants have their blood pressure measured and their contact details updated if necessary. At the final twelve month follow-up, anthropometry is repeated and blood pressure measured, a follow-up questionnaire is administered by a research assistant and clinical records are reviewed to capture intervening clinical events and changes in medical management. Participants who miss their scheduled visit at 12 months are actively traced by community-based research staff; if cause for non-attendance is hospital admission or death, then hospital records or death certificate data are obtained.

### Sample size calculations

The trial is powered on the primary outcome measure and based on a comparison of mean blood pressures between the usual care group and each of the intervention groups at 12 months.

A decrease in systolic blood pressure of 5 mm Hg is associated with clinically important reduction in the relative risk of stroke and coronary heart disease events. [4] Based on a study population similar to that expected for the StAR trial population we used the standard deviation (SD) of systolic blood pressure (22.0 mm Hg) to calculate the required sample size. [9]

With a proposed sample size of at least 1215 participants (no fewer than 405 for each group) and a 1:1:1 allocation ratio, the trial will have power of 90% with an alpha of 0.05 (two-sided), to detect an absolute mean difference of 5 mm Hg in the change in systolic blood pressure at 12 month from baseline, allowing for up to 20% loss to follow up.

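### 405 per group gives about 90% power only with complete follow-up; with the stated 20% loss, the plan's own inputs give about 82%

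*Protocol article*

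**What the plan says.** Everything needed is under *Sample size calculations* in the protocol article. On the variability, "we used the standard deviation (SD) of systolic blood pressure (22.0 mm Hg) to calculate the required sample size". On the size, "With a proposed sample size of at least 1215 participants (no fewer than 405 for each group) and a 1:1:1 allocation ratio". On the operating characteristics, "the trial will have power of 90% with an alpha of 0.05 (two-sided"), and the target is "to detect an absolute mean difference of 5 mm Hg in the change in systolic blood pressure at 12 month from baseline". The sentence ends with the attrition allowance: "at 12 month from baseline, allowing for up to 20% loss to follow up". The comparison being powered is each intervention group against usual care.

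The section gives no SD of change, no correlation between baseline and 12-month pressure, and no reduction in variance for covariate adjustment. *Statistical methods* plans a mixed-effects model on the 6- and 12-month readings, adjusted for baseline systolic pressure and the minimisation factors. The sample size section does not refer to that model.

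**The concern.** A number that allows for 20% loss should be about a quarter larger than the evaluable number required (1/0.8 = 1.25). Here the number to be enrolled almost equals the evaluable number that the stated SD, difference, alpha and power require. Either the allowance was described but not applied, or the calculation used a smaller variance that is not reported.

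At stake is how a null result is read. The section itself presents 5 mm Hg as a clinically important reduction. A reader told that the trial has 90% power even after 20% loss will take a non-significant comparison as fairly strong evidence against an effect of that size. On the stated calculation, the chance of missing it is about 18% per comparison, not 10%.

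A smaller point adds to the ambiguity: the SD quoted is that of systolic pressure itself, while the target is a difference in change from baseline. Which SD applies depends on the analysis and on a correlation that is not given.

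**Working it through.** **Inputs, all from *Sample size calculations*:** SD 22.0 mm Hg; difference 5 mm Hg; two-sided alpha 0.05 (z = 1.960); power 90% (z = 1.2816); 405 per group; 20% loss.

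**1. Evaluable number required**

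n = 2 × (1.960 + 1.2816)² × 22² / 5² = 406.8, so 407 per group.

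**2. The plan's figure with complete follow-up**

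With 405 per group, SE = 22 × √(2/405) = 1.546 and 5/1.546 = 3.234. Power = Φ(3.234 − 1.960) = 89.9%. The stated 90% is therefore reproduced when nobody is lost.

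**3. The plan's figure with the stated loss**

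405 × 0.8 = 324 per group. SE = 22 × √(2/324) = 1.728 and 5/1.728 = 2.893. Power = Φ(2.893 − 1.960) = 82.5%, or 82.3% with the noncentral t. The stated 90% is not reproduced; the shortfall is about 7.5 percentage points.

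| Loss | Power from 405 randomised per group (SD 22, unadjusted) |
|---|---|
| 0% | 89.9% |
| 5% | 88.3% |
| 10% | 86.6% |
| 15% | 84.7% |
| 20% | 82.5% |

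**4. What 20% loss implies at 90% power**

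- Detectable difference at 324 per group: 1.728 × (1.960 + 1.2816) = 5.6 mm Hg.
- Number to randomise for 5 mm Hg: 407/0.8 = 508.75, so 509 per group and 3 × 509 = 1527 in all. The cruder inflation 407 × 1.2 gives 489 per group, which does not match 405 either.

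**5. What would make 405 correct**

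The SD at which 324 per group gives 90% power is √(324 × 25 / (2 × 10.507)) = 19.6 mm Hg, where 10.507 = (1.960 + 1.2816)².

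- With baseline adjustment, the residual SD is 22 × √(1 − r²), so r must be at least √(1 − (19.63/22)²) = 0.45.
- With unadjusted change scores, the SD is 22 × √(2(1 − r)), so r must be at least 1 − (19.63/22)²/2 = 0.60.

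The documents give no correlation, so these are assumed values:

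| Assumed r | Power at 324, baseline-adjusted | Power at 324, unadjusted change |
|---|---|---|
| 0.3 | 85.8% | 68.6% |
| 0.4 | 88.4% | 75.2% |
| 0.5 | 91.6% | 82.5% |
| 0.6 | 95.1% | 89.9% |

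If 22.0 were itself the SD of change, step 3 would apply unaltered and power would still be 82.5%.

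**6. Other readings**

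A one-sided 5% test gives 89.4% power at 324 per group, which would fit, but the text says two-sided. A target of 80% power needs 304 evaluable, or 380 after inflation for loss, which does not match 405.

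**The case against.** The best reply is that step 3 is not the planned analysis. The primary model adjusts for baseline systolic pressure, and with a correlation of 0.45 or more, 324 per group does give 90%. The number 405 even fits that account: 406.8 × (1 − 0.45²) = 324.4, and 324.4/0.8 = 405.6. The full protocol may contain such an assumption, and the article may have condensed it away.

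It can also be said that 20% is an upper bound on loss and 405 a lower bound on size, that participants who miss the 12-month visit are traced, and that the mixed model keeps the 6-month readings of those without a 12-month value. Finally, randomisation makes the difference in mean change and the difference in mean 12-month pressure estimate the same quantity, so quoting the raw SD is not in itself an error and is conservative under baseline adjustment.

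Much of this stands. Actual power may be adequate, and the document does not settle whether the allowance was left out or a variance assumption was left unprinted. The SD remark matters only because the correlation is missing. None of it rescues the printed claim. The section says that the SD of systolic pressure was used, mentions no adjustment, and asserts 90% power at the upper bound of loss, so that bound is where the claim must be tested. Condensing may explain a missing detail, but here the article makes a specific statement that its own figures contradict.

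**Conclusion.** The concern holds. On the stated inputs, 405 per group gives 89.9% power with complete follow-up and about 82% with 20% loss. The claim of 90% power with the loss allowed for is wrong as written.

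The 82%, and the 18% risk of missing a true 5 mm Hg effect, belong to the calculation as stated: SD 22, no baseline adjustment, the full 20% lost in each group, and each intervention compared with usual care at two-sided 5%. Under the planned adjusted model, power at that loss would be 85.8% to 95.1% for assumed correlations of 0.3 to 0.6, and reaches 90% at about 0.45. The finding is that the power statement is unsupported, not that the trial is certainly too small.

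**What to change.** Correct the statement in *Sample size calculations* in one of two ways:

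- **Keep the unadjusted calculation and report it accurately.** For example: *A total of 1215 participants gives about 90% power to detect 5 mm Hg with complete follow-up and about 82% with 20% loss (SD 22 mm Hg, unadjusted comparison).*
- **Base the claim on the planned model.** State that the calculation is for the baseline-adjusted comparison, and give the assumed baseline to 12-month correlation with its source. It must be about 0.45 or more for 324 per group to give 90%.

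The second is appropriate only if the correlation was assumed at the design stage or can be supported from data other than this trial's outcome data.

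The cost is one sentence. No extra participants are needed, and neither the design nor the analysis changes. The stated power becomes less favourable, or it comes to rest on an explicit assumption that a reader can judge.
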